**2.3 What are the planned trial interventions?**

**2.3.1 All participants.** Data to generate Vesikari scores([20](#_ENREF_20)), a validated measure of gastroenteritis severity, will be collected at enrollment, and all study participants will be weighed and measured using calibrated apparatus. Percent dehydration will be abstracted from the paediatric team admission note (subjective dehydration) and will also be calculated comparing weight nadir in hospital to weight at discharge from hospital (objective dehydration). All participants will have a rectal flocked swab taken at enrollment within 18 hours of admission. Most of these children will not be started on antimicrobials at admission, as per current Princess Marina Hospital and World Health Organization standards, excepting children with severe acute malnutrition. Rehydration procedures will be decided by the attending physician; as per Princess Marina Hospital dehydration protocols, all those with severe dehydration receive intravenous rehydration with isotonic fluids and those with mild-moderate dehydration receive WHO-standard oral rehydration solution (ORS). It is standard of care at Princess Marina Hospital to also provide zinc treatment for gastroenteritis.

**2.3.2 Rapid testing and targeted antimicrobial therapy plus probiotic therapy arm.** These participants will be started on *Lactobacillus reuteri* within 24 hours of enrollment**.** All of these participants’ rectal swabs will be processed using our novel diagnostic techniques and resulted within 48 hours. It will be recommended to the attending physician that *Shigella,* ETEC, and *Campylobacter* infections be treated with azithromycin, and *Cryptosporidium* infections be treated with nitazoxanide. It will also be recommended that antimicrobials will be started as soon as possible, preferably on the day the test results become available, and antimicrobials will be provided free of charge. Probiotic therapy will be continued until the measurement of the primary outcome, 2 months post-enrollment.

**2.3.3 Rapid testing and targeted antimicrobial therapy plus placebo therapy arm.** These participants will be started on placebo therapy within 24 hours of enrollment and will have rectal swabs processed rapidly (see 2.3.2). Placebo therapy will be continued until the measurement of the primary outcome, 2 months post-enrollment.

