**2.13 What is the proposed type of analysis?**

The principal analysis will be intention-to-treat, i.e. all participants will be analyzed in the groups to which they were randomized, regardless if they received the appropriate antimicrobials (for those in the rapid swab analysis groups) or if they were adherent to the probiotic treatment (for those in the relevant groups). As the primary outcome (mortality) is binary, the chi-square test will be used. The chi-square test will also be used to interpret the following secondary outcomes: presence of stunting at 60-day followup, 7-day mortality, recurrence of acute diarrhoea during the 60-day followup period, re-presentation to a medical professional or readmission to Princess Marina Hospital because of acute diarrhoea in the 60-day followup period, and detectable HIV viral load within 6 months of enrollment. Analysis of covariance or logistic regression will be used to analyze the following secondary outcomes: height z-score at 60 days adjusted for initial height, weight z-score at 60 days adjusted for initial weight, and environmental enteropathy score at 60 days. Survival analysis will be used to analyze the following secondary outcomes: length of stay in hospital, number of days with at least three watery stools, and number of days of fever in hospital. Secondary analyses will attempt to control for the time to initiation of appropriate antimicrobial therapy and the time to initiation of probiotic therapy. Statistical analysis will be conducted using STATA 11.0 (College Station, TX).

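### Initial weight, whose fluid error depends on an unfixed weighing time, is the only covariate for 60-day weight z-score; baseline dehydration and Vesikari score, already collected, are named as covariates nowhere

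*Protocol*

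**What the plan says.** **Weight.** Protocol section 2.13 states "Analysis of covariance or logistic regression will be used to analyze the following secondary outcomes" and lists among them "weight z-score at 60 days adjusted for initial weight". Section 2.8.2 builds the same single covariate into the outcome definition.

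**Length of stay.** Section 2.13: "Survival analysis will be used to analyze the following secondary outcomes: length of stay in hospital". No covariate is named.

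**Other adjustment in 2.13.** "Secondary analyses will attempt to control for the time to initiation of appropriate antimicrobial therapy and the time to initiation of probiotic therapy". Both of these times arise after randomisation.

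**What is collected at baseline (2.3.1).** Vesikari data "will be collected at enrollment, and all study participants will be weighed and measured using calibrated apparatus". Also: "Percent dehydration will be abstracted from the paediatric team admission note (subjective dehydration"). A second dehydration value is "calculated comparing weight nadir in hospital to weight at discharge from hospital (objective dehydration"), so it is known only at discharge.

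**Timing (2.3.1).** "All participants will have a rectal flocked swab taken at enrollment within 18 hours of admission". Weighing is part of enrolment, but nothing says whether it comes before, during or after rehydration.

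**Severity elsewhere.** Section 2.14, on subgroups, says the trial will explore the influence of initial severity. It names no variable, model or outcome. Section 2.5 stratifies randomisation by severe acute malnutrition.

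**The concern.** The protocol itself reads in-hospital weight change as fluid: that is how section 2.3.1 defines objective dehydration. Section 2.13 then uses one early in-hospital weight as the growth baseline. That weight equals the rehydrated weight minus whatever deficit remains when the child is put on the scale. The remainder depends on the initial deficit and on how much rehydration has already taken place. Turning initial weight into a z-score would carry the same error.

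An error-laden baseline explains less of the 60-day weight, so the covariance model keeps more residual variance than it needs to. An available baseline measure of the deficit could remove part of it. Likewise, a baseline severity score is the obvious candidate to explain some of the spread in length of stay.

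The stake is limited but real. Section 1.2 wants this pilot to supply data for the larger trial's sample size, and section 2.6 counts growth among the important outcomes. A noisier growth model than necessary gives a larger variance to plan from.

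**Working it through.** The protocol gives no SD, effect size or precision for weight or length of stay, and the sample of 100 is justified on feasibility alone (2.11). There is therefore no stated figure to reproduce. The size of the effect is worked out under assumptions.

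**Weight: inputs**
- From the protocol: 100 children allocated 1:1:1:1 (2.5, 2.11), so about 50 v 50 for rapid v delayed testing. The probiotic comparison is somewhat smaller, because children with severe acute malnutrition are not randomised to it.
- Assumed: SD of weight z-score s = 1.2; correlation of rehydrated baseline with 60-day z-score ρ = 0.8 or 0.9; between-child SD of the deficit at weighing 2%, 3% or 4% of body weight; one z-score about 11.5% of body weight; deficit independent of rehydrated weight and of the 60-day value; reliability of admission-note dehydration r = 0.5.

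**Weight: formulas**
- Deficit SD in z units: e = (percent SD)/11.5.
- Residual variance with initial weight only: s² − (ρs²)²/(s² + e²).
- With admission dehydration added, only the unexplained part of the deficit remains: s² − (ρs²)²/(s² + e²(1 − r)).
- Standard error (SE) of the group difference: √(2 × variance/50).

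**Weight: example** (ρ = 0.9, SD 3%)
- e = 3/11.5 = 0.261, e² = 0.068, s² = 1.44, (ρs²)² = 1.296² = 1.680.
- Initial weight only: 1.44 − 1.680/1.508 = 0.326, SE 0.114.
- With dehydration: 1.44 − 1.680/1.474 = 0.301, SE 0.110.
- Reduction in variance: 7.9%.

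| ρ | Deficit SD | Variance, weight only | Variance, + dehydration (r = 0.5) | Reduction | SE before → after |
|---|---|---|---|---|---|
| 0.8 | 2% | 0.537 | 0.528 | 1.7% | 0.147 → 0.145 |
| 0.8 | 3% | 0.560 | 0.540 | 3.6% | 0.150 → 0.147 |
| 0.8 | 4% | 0.590 | 0.556 | 5.8% | 0.154 → 0.149 |
| 0.9 | 2% | 0.298 | 0.286 | 4.0% | 0.109 → 0.107 |
| 0.9 | 3% | 0.326 | 0.301 | 7.9% | 0.114 → 0.110 |
| 0.9 | 4% | 0.364 | 0.321 | 11.9% | 0.121 → 0.113 |

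With no covariate at all the SE is √(2 × 1.44/50) = 0.240, so initial weight alone already does most of the work. If dehydration were measured almost without error, the reductions would be 3.5-24.8%; a chart estimate will not reach that.

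**Effect of partial rehydration.** If half of every child's deficit is corrected before weighing, a 4% SD at admission becomes 2% at weighing. The reduction then falls from 11.9% to 4.0% (ρ = 0.9) or from 5.8% to 1.7% (ρ = 0.8). If the corrected fraction also differs between children, the admission value tracks the error less well and the gain is smaller still.

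**Chance imbalance.** With a deficit SD of 0.3 z, the group difference in deficit has SE 0.3 × √(2/50) = 0.06 z. It enters the adjusted estimate multiplied by the baseline slope, ρs²/(s² + e²) = 1.296/1.53 = 0.85 at ρ = 0.9, giving about 0.05 z. This is already part of the SEs in the table.

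**Length of stay** (linear-model approximation; R² assumed; deliberately cautious penalty of two degrees of freedom)
- Variance ratio = (1 − R²) × 97/95; effective N = 100/ratio.

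| R² | SE ratio | Effective N |
|---|---|---|
| 0.02 | 1.00 | 100 |
| 0.05 | 0.985 | 103 |
| 0.10 | 0.959 | 109 |
| 0.20 | 0.904 | 122 |

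For a standardised difference of 0.5 with 50 v 50, power is 70.5% unadjusted, 75.0% at R² = 0.10 and 79.8% at R² = 0.20 (no degrees-of-freedom penalty). The planned method is survival analysis. In a Cox model the SE of the log hazard ratio does not shrink in this way; adjustment shows up mainly as power. The table is therefore only a rough guide.

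**The case against.** **A full covariate list belongs in the statistical analysis plan, which is not shown.** This stands in part: silence in 2.13 is not a decision against other covariates, and adjusting for the baseline measure is a sound choice. But the weight model is stated, with its covariate, in two sections, and can be improved as stated.

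**Severity is already covered.** A reader might infer that the plan ignores severity. It does not: section 2.14 leaves room for covariate use, and section 2.5 stratifies by severe acute malnutrition. Still, an intention to explore, under a subgroup heading and with no model named, does not pre-specify an adjustment.

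**The children may no longer be dehydrated when weighed.** This stands. It is tempting to say that initial weight is measured in children who are still dehydrated, but the protocol does not say so. Enrolment may come up to about 18 hours after admission with rehydration under way, and objective dehydration is built on the in-hospital nadir, not on the enrolment weight. What the document supports is that the deficit at weighing is uncontrolled. The same fact weakens the remedy, since admission-note dehydration describes admission and not the moment of weighing.

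**Bias.** A reader might infer that an imbalance in dehydration passes straight into the treatment estimate. Under randomisation the covariance estimate is unbiased; imbalance enters scaled by the slope and is already in the SE.

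**Length of stay.** It is tempting to say that a score explaining a given share of variance saves that share. That is a linear-model rule and does not carry over to a survival analysis.

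**Proportion.** These are secondary outcomes in a pilot sized for feasibility. No feasibility criterion in 2.10 depends on them. This stands and sets the weight of the point.

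**Conclusion.** The point holds as a minor improvement, not as an error in the plan. Initial weight is the only covariate named for 60-day weight z-score, its fluid error is uncontrolled because weighing is not timed against rehydration, and two baseline measures collected on every child are named as covariates in no comparison.

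The direction is clear; the size is modest and wholly dependent on assumed SDs, correlations and reliability. For length of stay the gain could be nil. The validity of the planned comparisons is not in question. The practical benefit lies mostly in a cleaner growth variance for designing the follow-up trial.

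**What to change.** In section 2.13:
- Pre-specify admission-note percent dehydration as an added covariate in the 60-day weight z-score model. Do not use the objective value: it depends on discharge weight, which is measured after randomisation and may be affected by treatment.
- Pre-specify the enrolment Vesikari score as a covariate in the length-of-stay model.
- Report each adjusted result beside the result without the added covariate, so that the pilot shows what the adjustment gains.

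In section 2.3.1, have the case report form record the time of the initial weighing and the time rehydration started. This is a recording item only and changes nothing in care.

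**Cost.** One or two sentences, one degree of freedom per model and two recorded times; both covariates are already collected. If a Cox model is used for length of stay, the adjusted hazard ratio is conditional on severity and not marginal, so the two results estimate different quantities and should be labelled accordingly.

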**2.14 Will there be any sub-group analysis?**

Children with severe acute malnutrition are functionally significantly immune compromised, and are very different than those without; consequently, we will attempt to analyze this group separately, though definite conclusions will be difficult to make if numbers are small. Mortality in this sub-group is much higher than in well-nourished children, so even if the benefits of the experimental interventions are less, it is important to include them in this trial. We will also explore the impact of HIV infection/exposure and the severity of the initial presentation on the analysis. We should also note that preliminary data suggest that the benefit of probiotic therapy is much greater in children with viral gastroenteritis; consequently, we will be analyzing those separately from those with no detected viral infections.

**2.15 Potential problems and alternative strategies.**

Our biggest concern with this study is avoiding loss to follow-up; this is why to be eligible the potential participant must reside within a 50 km radius of Princess Marina Hospital, be relatively stable, and have some means by which the research assistant can contact them. We will be providing simple incentives to encourage families to accept follow-up.

It will also be of prime importance to minimize the delay between rectal swab acquisition, finalizing the result, and initiating appropriate antimicrobial therapy (if applicable) in the rapid swab result groups. We are currently optimizing laboratory procedures and flow-through at the Botswana National Health Laboratory using already-developed molecular assays and an ABI 7500 platform. Should there be unacceptable delays in specimen processing, we will explore alternative platforms.

**2.16 Ethical considerations**

**2.16.1 Risks to the safety of participants involved in the trial.**

There should be very little risk to study participants. The use of the flocked rectal swab itself – the most invasive study procedure – should pose negligible risk; the process is very similar to that used for measuring rectal temperatures, and to date, we have acquired over 500 of these specimens without a single complication. The other risk associated with the study would be breach of confidentiality, and we will take all standard precautions to guard against that: the key document linking participant names, addresses, and other direct identifiers will be kept in a locked cabinet (and a password-protected computer) in a locked office to which only the local PI and/or study nurse will have access; the case report forms with study data will be labeled only with the study ID; and no information containing direct identifiers will ever be sent electronically. Stool samples labeled with study IDs (and no direct identifiers) will be sent to Canada for enzyme testing but no genetic testing will be done.

Probiotic therapy – the administration of viable ‘good’ bacteria to patients – is not the current standard of care in Botswana for the treatment of gastroenteritis. However, as detailed previously in this protocol, numerous studies done in both higher-income and lower-income countries have documented clinically significant improvements in presumed infectious gastroenteritis associated with probiotic use and no significant adverse reactions have been observed after treatment of thousands of immunocompetent children. Children with severe acute malnutrition are obviously not functionally immunocompetent, so they will not be eligible for probiotic treatment in this study.

It will be explained to participants that they have much to potentially gain by being in the study; should our testing detect a treatable pathogen, this information will be communicated to the attending physician in a timely manner. Furthermore, in many cases, the study will provide drug therapy free of charge to the study participant; azithromycin should be superior to nalidixic acid, currently the standard of care for the treatment of bacillary dysentery at Princess Marina Hospital.

**2.16.2 Informed consent**.

Informed consent will of course be a necessary prerequisite to enrollment in the study. The research nurse will explain the trial in detail on the paediatric medical ward at Princess Marina Hospital to the caregiver that is present with the child. As all of our patients will be younger than five years in age, and there are no real invasive procedures associated with the study protocol, we will not be seeking assent from the child participants. Consent will be sought for the repeat visits at 12 months post enrollment, and to analyze the bacterial populations (microbiome analysis) of the stool sent to McMaster University, even though those are not key aspects of the trial; we do not yet have funding for these components, but it would be most appropriate to ask for consent up front.

**3.0 TRIAL MANAGEMENT**

**3.1 Day-to-day management of the trial.**

The coordinating centre will be at the Botswana UPenn-Partnership. The local PI, [name], will have ongoing communication with the research nurse to monitor enrollment, verify thorough and complete data collection, and troubleshoot issues. All microbiology testing will take place at the National Health Laboratory (NHL) under the supervision of [name]. The study PI will arrange brief teleconferences with BUP and NHL personnel to monitor study progress on a weekly basis, or as frequently as is needed to ensure smooth functioning of the trial. Paper case report forms will be digitized on a regular basis by BUP support staff or by the research nurse, as needed. All forms containing direct identifiers will be maintained under lock and key or in a password-protected computer in a locked office, but other data will be transmitted to McMaster University using a REDCap database.

**3.2 Quality control and assurance.**

An audit process will be completed after each 25 participants enrolled by the research nurse, other research assistants, or investigators. 5 records (per each 25) will be selected randomly to verify the following indicators: eligibility, consent forms, signatures, timing of specimen collection, timing of results, timing of antimicrobial administration (if applicable), collection of data relating to outcomes at the time the record is verified, and missing data. At these times a formal review of the case report forms with the research nurse will be undertaken to determine if improvements need to be made. The health records department at Princess Marina Hospital will be contacted to verify on a monthly basis the number of patients of the appropriate age admitted with acute gastroenteritis.

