**2.7 What is the proposed frequency and duration of follow-up?**

The research assistant will contact the participant 7-14 days after discharge from hospital to ensure that the caregivers remember the timing of the second follow-up visit and to answer any relevant questions about the study. The research assistant will then contact the participant again 60 days after enrollment to assess the primary outcome and weigh and measure the participant, if applicable. It would be optimal to have another follow-up visit approximately 12 months after enrollment; this may not be feasible with the funds we have acquired for this project, but we will ask participants for consent to approach them should moneys become available.

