**2.8 What are the proposed *clinical* outcome measures?**

**2.8.1 Primary clinical outcome.** The primary outcome is mortality. If the participant dies prior to the 60-day followup, the research assistant will determine the date of death as accurately as possible.

**2.8.2 Other clinical outcomes.** Secondary outcomes will include the following: weight z-score at 60-day followup adjusted for initial weight; height z-score at 60-day followup adjusted for initial height; presence of stunting at 60-day followup; length of stay in hospital; number of days with at least three watery stools; number of days of fever in hospital; 7-day mortality; recurrence of acute diarrhoea during the 60-day followup period; re-presentation to a medical professional because of acute diarrhoea during the 60-day followup period; readmission to a paediatric medical ward during the 60-day followup period; HIV viral load (detectable/undetectable) at the next assessment within 6 months of enrollment, for those participants that are HIV positive; and environmental enteropathy score([21](#_ENREF_21)) (composite of faecal alpha-1 antitrypsin, neopterin, and myeloperoxidase) at 60 days.

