**2.9 How will the *clinical* outcome measures be measured at follow up?**

**2.9.1 Mortality.** Mortality will be ascertained by the research assistant, whether in hospital or after discharge.

**2.9.2 Secondary clinical outcomes**. Data related to secondary clinical outcomes associated with the participant’s stay in hospital (number of days of 3+ watery stools, number of days of fever, length of stay) will be abstracted from the patient chart (both physician and nursing notes) at discharge. The remaining secondary clinical outcomes will be assessed at the 60-day followup visit; the research assistant will use a calibrated scale and stadiometer to obtain precise anthropomorphic measures.

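### Readmission is defined for any cause but tested only for diarrhoea at one hospital, and the visible protocol sets no serious-event enquiry or review for a live probiotic given for 2 months

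*Protocol*

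**What the plan says.** **Readmission.** Section 2.8.2 lists as a secondary outcome "readmission to a paediatric medical ward during the 60-day followup period". The chi-square list in section 2.13 instead names "re-presentation to a medical professional or readmission to Princess Marina Hospital because of acute diarrhoea in the 60-day followup period".

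**Product and population.** Under sections 2.3.2 to 2.3.4, probiotic or placebo continues until 2 months after enrolment. Section 2.16.1 describes the probiotic as viable bacteria and argues its safety from published use in immunocompetent children. It keeps children with severe acute malnutrition off the product because they are not functionally immunocompetent. Section 2.2.1 does not exclude children with HIV and sets no HIV-related bar to the product.

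**Follow-up.** Section 2.7 gives the purpose of the 7-14 day contact: "to ensure that the caregivers remember the timing of the second follow-up visit and to answer any relevant questions about the study". If a child dies, section 2.8.1 says "the research assistant will determine the date of death as accurately as possible". Under section 2.9.2, in-hospital outcomes are abstracted from the chart at discharge, and "The remaining secondary clinical outcomes will be assessed at the 60-day followup visit".

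**Oversight.** Under section 3.1 the local principal investigator "will have ongoing communication with the research nurse to monitor enrollment, verify thorough and complete data collection, and troubleshoot issues", and teleconferences are held "to monitor study progress on a weekly basis, or as frequently as is needed to ensure smooth functioning of the trial". The audit in section 3.2 reads "5 records (per each 25) will be selected randomly to verify the following indicators: eligibility, consent forms, signatures". Its list goes on to the timing of specimens, results and antimicrobials, outcome data and missing data.

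**The concern.** Two things look wrong.

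First, the protocol defines one readmission outcome and analyses a narrower one. The part left out includes readmission for serious infection, which is the kind most relevant to the safety of a live product.

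Second, apart from events that happen to be outcomes, the visible text never says that anyone asks about serious adverse events, records why a child died, judges whether an event is related to the product, or decides whether the product should continue. These are matters of trial conduct. A statistical analysis plan can say how events are reported, but it cannot supply answers that nobody asked caregivers for.

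Section 1.2 says the pilot will assess every aspect of the later trial, including outcome methods and event rates, and will test the data collection forms. Cause of death and serious events by product group are things it could learn cheaply and, as written, is not set up to learn.

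**Working it through.** The protocol gives no figure on this point, so there is none to reproduce. The check sets the sections side by side.

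**Step 1. The readmission outcome.**

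| Element | Section 2.8.2 | Section 2.13 |
|---|---|---|
| Cause | any | acute diarrhoea |
| Place | any paediatric medical ward | Princess Marina Hospital |
| Window | 60 days | 60 days |
| Form | separate from re-presentation | joined to re-presentation by an 'or' |

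Cause and place give four kinds of readmission:
- Diarrhoea, Princess Marina: meets both definitions.
- Diarrhoea, another hospital: meets 2.8.2 but not the readmission wording in 2.13. It would probably still count there as re-presentation to a medical professional.
- Other cause, Princess Marina: meets 2.8.2 only.
- Other cause, another hospital: meets 2.8.2 only.

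The material loss from the stated test is therefore all non-diarrhoeal readmissions. The restriction to one hospital matters less, but it is still a mismatch.

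**Step 2. Following a serious event through the stated steps.**
- *In hospital.* Chart abstraction at discharge covers watery-stool days, fever days and length of stay. Death is ascertained by the research assistant. Other serious events may be in the notes but are not listed for abstraction.
- *After discharge, early.* The 7-14 day contact has no stated health enquiry.
- *Day 60.* Mortality, growth, diarrhoea recurrence, re-presentation for diarrhoea, and readmission are assessed. A serious infection is reached if it led to readmission. A suspected reaction to the product that did not lead to death, readmission or diarrhoea matches no listed outcome.
- *Death.* The date is recorded. No cause is asked for.
- *Review.* The contacts in section 3.1 concern enrolment, data completeness, troubleshooting and progress. No one is named to judge relatedness or to decide on continuing the product.

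**Step 3. What the pilot could show about rates (context only).** With 100 children allocated 1:1:1:1, at most about 100 × 2/4 = 50 receive probiotic. The number is lower in practice, because severely malnourished children are not randomised to the product. If none of 50 had a serious event, the one-sided 95% upper limit would be 1 − 0.05^(1/50) = 5.8%. The pilot cannot establish safety by counting. The case for collection is to notice and act on individual events and to test the forms, not to estimate a rate precisely.

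**The case against.** The strongest reply is that the second half of the point is an absence, in a file with gaps. Consent pages are not shown, only the headings of Appendices 1 and 3 appear, and the case report forms are not available. Safety wording may sit there. This stands as a limit: the point covers the visible text only. It does not touch the readmission mismatch, which lies between two visible sections.

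Several other replies are fair:
- The audit does check outcome data, and so the capture of deaths, readmissions and fever. Its list shows the safety gap only indirectly; sections 2.7, 2.8, 2.13 and 2.16.1 are the real basis.
- Chart abstraction at discharge gives a source for in-hospital events.
- Ongoing contact between the local principal investigator and the research nurse, with weekly calls, lets problems be raised. It assigns no one to ask, judge or act.
- The review cited in section 1.1 pooled 63 studies (n=8014) and reported no significant or serious adverse reactions. Product-related harm is probably rare.

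Two stronger readings are tempting, and the documents do not support them. A reader might infer that data on non-diarrhoeal readmissions would be lost. They would not: section 2.8.2 makes any-cause readmission an outcome and section 2.9.2 has it assessed at day 60, so it could be tabulated by group. A reader might also infer that children with HIV face a known added risk and should be kept off the product. The protocol gives no evidence of that, and section 2.14 plans to explore the impact of HIV. What stands is narrower: the stated rationale does not clearly cover these children, so their serious events should be asked about.

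**Conclusion.** Both parts hold and should be corrected.

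(a) Sections 2.8.2 and 2.13 contradict each other on readmission, by cause and by hospital. This rests on the wording alone and needs no assumption. The effect is that collected non-diarrhoeal readmissions are left out of the stated analysis.

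(b) The visible text gives a live product for 2 months with no stated serious-event enquiry, no cause of death and no assigned reviewer. This assumes that the unseen consent and appendix material does not fill the gap; if it does, a cross-reference would be enough.

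No harm rate or delay in detection is put on this. The protocol gives no length of stay from which to time the early contact, and its own evidence points to rare harm. The weight comes from how little the correction costs.

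**What to change.** 1. **Section 2.13:** analyse readmission for any cause to any paediatric medical ward, as section 2.8.2 defines it, with diarrhoea readmission as an additional breakdown. State whether re-presentation and readmission are separate outcomes or one combined outcome.
2. **Sections 2.7 and 2.9:** at discharge, at the 7-14 day contact and at day 60, the research assistant records serious adverse events and the probable cause of any death or readmission.
3. **Section 3.1:** the local principal investigator judges relatedness to the product, and these events become a standing item of the existing weekly call.
4. **Reporting:** list serious events by product group among children randomised to probiotic or placebo, with HIV status shown.

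The cost is a few sentences of amendment, one extra case report form page and a few minutes at contacts and calls already planned. Item 1 costs nothing. Sample size, recruitment and the blocked 1:1:1:1 randomisation are unchanged, and no new committee is needed.
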